#### Control group

2.5.3

Subjects in the self-exercise group (control group) will receive instructions on how to perform the exercises from a physiotherapist. The exercise program contains knee range of motion exercise, quadriceps setting exercise (10 minutes, 3 times during a day), straight leg raise exercise (5 minutes, 10 times during a day), ankle pump exercise (4 minutes, 10 times during a day), a standing side-to-side weight shift exercise (2 minutes, 3 times during a day), partial squat with chair exercise (2 minutes, 3 times during a day), and heel raise exercise (2 minutes, 3 times during a day). All exercises in the control group are the same as in the intervention group, except the use of wearable device. Consequently, biofeedback using surface EMG and electrical stimulation will not be available. Training materials will be provided, which will include an illustration of exercises with pictures. An exercise logbook will also be provided to all subjects in the self-exercise group to record exercise frequency and duration.

### Assessment

2.6

The primary and secondary outcomes will be assessed at baseline, 2 weeks, 4 weeks, and 6 weeks postintervention (see Fig. 1). All participants will be requested to complete follow-up assessments, except for those who will withdraw or will be withdrawn from the study. Those subjects will be asked to identify reasons for withdrawal. The assessment will last approximately 1 hour, with regular breaks provided to mitigate fatigue and burden.

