**Methods and analysis::**

This is a protocol proposal for a prospective, single-center, randomized, controlled study. We plan to recruit adults discharged after ACL reconstruction; the recruited subjects will be randomly allocated to 1 of 2 groups, using a computer-generated randomization method: the intervention (n = 20) or control group (n = 20). The intervention group will receive a 6-week home-based rehabilitation program using smart wearable device. The control group will undergo a 6-week self-exercise program as normal. The following outcomes will be assessed at baseline, 2 weeks, and 6 weeks post the 6-week intervention program: quadriceps strength of the affect side as measured by a dynamometer (primary outcome); range of motion; root mean square of quadriceps muscle using surface electromyography; knee function using questionnaire; quality of life; subject's satisfaction score using questionnaire; frequency and duration of exercise; and knee pain. An intention-to-treat analysis will be conducted for the primary outcome.

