#### Primary outcome measures

2.6.1

Isokinetic strength testing will be performed using the dynamometer (Primus RS, BTE Technologies, Hanover, MD) at 6 weeks after the intervention. We will report the ratio (as a percentage) of knee extensor strength in the affected side to the unaffected side.

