### Harms and benefits

2.7

The medical device used in this study has the ability to measure the range of motion exercises, providing biofeedback through surface EMG measurement and neuromuscular electrical stimulation therapy. Each method is a commonly used treatment method for rehabilitation. The range of motion exercises and biofeedback through surface EMG measurement are not expected to be inconvenient or risky to the user. Neuromuscular electrical stimulation therapy is an electrical stimulation via medical electrodes. Since there are no reports that document any side effects or complications from neuromuscular electrical stimulation therapy, safety is not a major concern.^[26]^ Although there may be subjective discomfort in performing neuromuscular electrical stimulation therapy, the intensity can be controlled by the subject; instructions for controlling the intensity will be adequately explained. If there is a situation that requires termination of the therapy due to discomfort or other medical or subjective reasons, they will be withdrawn from the study immediately and reasons for discontinuation will be recorded.

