### Criteria for discontinuation

2.8

(1)Voluntary withdrawal of consent from the trial.(2)Aggravation of underlying disease.(3)Incompliance to intervention procedures (in this instance a specific reason must be recorded by the investigator).(4)Participation in the study is thought to interfere with other medical procedures.

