#### Sample size calculation

2.10.1

This study was designed as an exploratory trial with 2 groups – intervention and control groups – using a dynamometer. The sample size calculation was based on the difference in the quadriceps strength (torque, Nm) between the 2 groups from the baseline to the 6-week follow-up. The following formula was used to calculate the number of participants needed in each group:
 
[figure not shown]

According to a previous study, the difference in the means of 6-week quadriceps strength was 33, with a standard deviation of 30.^[27]^ Based on the 5% 2-sided significance level and 80% power, at least 14 participants are needed in each group. With an attrition rate of 30%, our study will recruit a total of 20 participants in each group.

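### Stopping therapy, and probably non-compliance, ends outcome collection, so the 6-week primary outcome is not sought from everyone the intention-to-treat analysis should include

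*Protocol article*

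**What the plan says.** Four statements have to be read together.

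- **Harms and benefits (2.7).** The trigger is "If there is a situation that requires termination of the therapy due to discomfort or other medical or subjective reasons". The consequence is that "they will be withdrawn from the study immediately and reasons for discontinuation will be recorded".
- **Criteria for discontinuation (2.8).** Criterion 3 is "Incompliance to intervention procedures (in this instance a specific reason must be recorded by the investigator"). The section does not say whether discontinuation refers to treatment or to the study.
- **Assessment (2.6).** "All participants will be requested to complete follow-up assessments, except for those who will withdraw or will be withdrawn from the study". From the people so exempted the plan seeks only an explanation: "Those subjects will be asked to identify reasons for withdrawal".
- **Abstract, Methods and analysis.** "An intention-to-treat analysis will be conducted for the primary outcome".

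Primary outcome measures (2.6.1) sets the timing of that outcome: "Isokinetic strength testing will be performed using the dynamometer (Primus RS, BTE Technologies, Hanover, MD) at 6 weeks after the intervention". Sample size calculation (2.10.1) allows for losses: "With an attrition rate of 30%, our study will recruit a total of 20 participants in each group".

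**The concern.** An intention-to-treat comparison needs the outcome of everyone randomised, or at least an attempt to obtain it. Here the protocol directs staff not to seek the 6-week strength test from people who are selected by what happened to them after randomisation. Three features of this trial make it unlikely that the selection acts equally in the two arms.

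- Discomfort from electrical stimulation can occur only in the device arm. The control programme has no stimulation (2.5.3).
- Exercise is logged automatically by the device in one arm and by a self-completed logbook in the other (2.5.2, 2.5.3), so non-compliance is detected differently.
- Compliance is what the device is meant to change. The Introduction hypothesises better motivation and compliance, and it cites compliance of only 35% to 76% with prescribed exercise, so non-compliance is not a rare event.

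At stake is the interpretability of the primary comparison. A value that was never measured cannot be recovered by any later analysis, and according to Trial status (2.2) data collection is already under way.

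**Working it through.** **1. The textual chain.**

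| Event | Consequence in the text | Follow-up assessment sought? |
|---|---|---|
| Therapy must be terminated (2.7) | Withdrawn from the study, explicitly | No (2.6) |
| Incompliance (2.8, criterion 3) | Discontinuation, object not stated | No, if discontinuation means the study |
| Consent withdrawn (2.8, criterion 1) | Leaves the trial | No, and rightly so |

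The first row is explicit. In the second, the study reading is the natural one, because criterion 1 in the same list concerns consent to the trial and 2.7 speaks of the study. The conflict with intention-to-treat stands on the first row alone.

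**2. The plan's own sample size.** Inputs from 2.10.1: difference 33, SD 30, two-sided 5%, power 80%, attrition 30%.

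- Standardised effect: 33/30 = 1.10.
- Normal formula: n = 2 × [30 × (1.960 + 0.842)/33]² = 12.97, so 13 per arm.
- Two-sample t-test: 14.00 per arm, with power 79.99% at 14.
- Attrition: 14/(1 − 0.30) = 20 per arm.

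Both stated figures (14 and 20) reproduce. The plan thus tolerates 20 × 0.30 = 6 participants per arm without a 6-week value. This is all-cause attrition, applied equally to both groups.

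**3. Illustration of the bias.** Assumptions that are not in the documents: no true effect, adherence and strength bivariate normal with correlation r, the least adherent removed, and a completers' t-test at 6 weeks. From the documents: SD 30 Nm and 20 per arm.

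If a fraction d of an arm with the lowest adherence is removed, the mean of those who remain rises by r × 30 × m(d), where m(d) = φ(z_d)/(1 − d) and z_d is the d-quantile of the standard normal. So

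bias = r × 30 × [m(d_device) − m(d_control)].

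With m(0.30) = 0.497 (6 of 20), m(0.15) = 0.274 (3 of 20) and m(0) = 0:

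- 6 v 3, r = 0.5: 0.5 × 30 × (0.497 − 0.274) = +3.3 Nm.
- 6 v 0, r = 0.5: 0.5 × 30 × 0.497 = +7.5 Nm.

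Simulation with exactly 20 per arm (40,000 trials per case) gives values close to the formula, slightly smaller because the arms are small:

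| Removed, device v control | Bias in Nm at r = 0.3 / 0.5 / 0.7 | False-positive rate (nominal 5%) |
|---|---|---|
| 6 v 6 | −0.1 / 0.1 / 0.0 | 5.2% / 5.8% / 7.0% |
| 6 v 3 | +1.9 / +3.3 / +4.6 | 5.5% / 6.9% / 9.2% |
| 3 v 6 | −1.9 / −3.3 / −4.5 | 5.5% / 6.8% / 9.0% |
| 6 v 0 (extreme) | +4.3 / +7.1 / +10.0 | 6.9% / 10.8% / 16.8% |

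Against the design difference of 33, the unequal cases run from about 6% (1.9/33) to 30% (10.0/33) in absolute size.

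**4. Scale.** These figures are in Nm, the scale of the sample size calculation. Section 2.6.1 reports the outcome as a percentage ratio of affected to unaffected side, so they do not carry over directly.

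**5. What full follow-up would give.** With effect and SD held fixed, t-test power is 92.4% with all 20 per arm assessed, against 80.0% with 14. Including poor adherers may shrink the effect itself, so the gain is an upper guide.

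**The case against.** The strongest objection is to any claim about direction. A reader might infer that the rule favours the device, because it would leave that arm with its good adherers. The documents do not support this. If the device improves compliance, as the Introduction hypothesises, a non-compliance rule removes more controls and works against the device. Stimulation discomfort and automatic logging push the other way. The net sign is unknown, and equal removal gives roughly zero bias. This objection stands.

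A reader might also take 6 v 0 as the planned loss. It is not: the 30% applies to each group and covers all causes.

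Third, it can be argued that poor adherers are not simply removed. Section 2.8 is ambiguous and asks for a specific reason, visits are used to encourage continued exercise (2.5), exercise frequency and duration is a secondary outcome (2.6.2), and participants control the stimulation intensity (2.7). This is fair. It means that the number affected cannot be known from the text, and that it would be too strong to say every non-complier is dropped. It does not touch the explicit rule for terminated therapy.

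Fourth, the mixed model in 2.11 may use earlier visits of people who leave, and missing-data methods may sit in an analysis plan that is not shown. Neither supplies a 6-week value that staff were told not to request.

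Finally, the trial calls itself exploratory. That lowers the stakes, but the protocol still announces a powered primary outcome, a superiority hypothesis and intention-to-treat.

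**Conclusion.** The point holds as an internal conflict with a real risk of bias, not as a demonstrated bias in a known direction. As written, sections 2.6 and 2.7, and on the natural reading 2.8, leave the 6-week primary outcome uncollected for participants selected on post-randomisation behaviour, while the Abstract promises intention-to-treat.

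Under the stated assumptions the distortion ranges from about −5 to +5 Nm when one arm loses 6 and the other 3. It is near zero when losses are equal, and reaches about +4 to +10 Nm, with a false-positive rate of about 7% to 17%, only in the extreme 6 v 0 case. The correlations and the split of losses are assumed. What can be said without them is that the bias could not be checked afterwards, because the outcomes needed to check it would not exist.

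**What to change.** Leave the clinical criteria for stopping therapy as they are. Reconcile 2.6, 2.7 and 2.8 with the intention-to-treat statement by distinguishing two events: discontinuing treatment and withdrawing from the study.

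- Say in 2.8 which of the two each criterion refers to.
- State in 2.6 and 2.7 that participants who stop the device or the exercises, or who are non-compliant, and who still consent, are asked to attend the assessments already scheduled, above all the 6-week strength test. The exception is an assessment that the investigator judges medically inappropriate.
- State that they are analysed in the group to which they were randomised.
- Continue to record reasons, separately for stopping treatment and for leaving the study, and report both by arm.

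The choice of model and of sensitivity analyses can be left to the analysis plan.

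The cost is a short amendment and some effort to bring back people who have stopped treatment. No extra visits and no larger sample are needed. The effect estimate may be diluted by non-adherence, which is inherent in an intention-to-treat comparison. As recruitment has begun, the change is worth most if made soon, including for participants already withdrawn whose 6-week visit is still ahead and who agree to attend.

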#### Primary outcome measures

2.6.1

Isokinetic strength testing will be performed using the dynamometer (Primus RS, BTE Technologies, Hanover, MD) at 6 weeks after the intervention. We will report the ratio (as a percentage) of knee extensor strength in the affected side to the unaffected side.

#### Secondary outcome measures

2.6.2

Active and passive range of motion of the kneeRoot mean square of surface EMG (measured bilateral rectus femoris, vastus medialis, and vastus lateralis)Knee function or deficiency using questionnaire (International Knee Documentation Committee score,^[21]^ Lysholm score,^[22,23]^ Knee outcome survey activities of daily living^[24]^)Quality of life (European Quality of Life-5 Dimensions 3-Level version^[25]^)Pain evaluation (visual analog scale)Satisfaction evaluation (5-point Likert scale)Frequency and duration for exercise using data from device or exercise logbook

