We propose an exercise program that will incorporate wearable technology with gaming components. The wearable device that will be used in this study (exoRehab, EXOSYSTEMS Inc., Seongnam, South Korea) can measure the range of motion and strength of the knee joint. This will allow us to measure whether the exercise program can increase the range of motion and strength of the knee after the operation. Moreover, this wearable technology will also make it possible to provide biofeedback to patients to verify whether there is sufficient contract to improve knee strength by measuring the surface electromyography (EMG). Previous studies have shown that biofeedback through the surface EMG improves not only knee extension,^[15]^ but also muscle strength of the quadriceps muscle.^[16]^ In addition to providing biofeedback to patients, it is possible to provide neuromuscular electrical stimulation and rehabilitation. Surface EMG-triggered neuromuscular electrical stimulation improves knee extension via increasing the active range of motion.^[17]^ Neuromuscular electrical stimulation therapy has also been shown in previous studies to show significant improvements in muscle strength and function outcomes of the quadriceps muscles.^[18,19]^

Information from the device can be used by doctors and therapists to enhance the understanding of patient compliance and progress of knee rehabilitation, which may be useful to determine a unique, personalized treatment goal tailored to each patient. We hypothesize that the incorporation of games and wearable technology into an exercise therapy program will improve patient motivation and compliance. This approach is expected to overcome and address the shortfalls of current rehabilitation treatment methods and promote a wave of new in-home rehabilitation programs.

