NMES will be performed with an isometric exercise in sitting position with the knee extended. The patient will first contract the quadriceps muscles, and electrical stimulation will begin only when the force exceeds 75% of MVIC. The device delivers biphasic rectangular waveform pulses (pulse duration 400 μs, frequency of impulses 2500 Hz, train of pulses frequency 50 Hz). A total of 15 contractions is sustained for 15 seconds (inclusive of 2 seconds ramp up and down), each with 50 seconds off time. The total time for 1 set of NMES is about 22 minutes. Patients will be recommended to use NMES at least 3 times a day, about 66 minutes per session. The amplitude should be set at an intensity that is high enough to produce a full, sustained contraction of the quadriceps with visual and/or palpable evidence. The initial intensity will be set for each subject when a physical therapist trains and explains the device and exercise. The stimulus intensity will be increased further to maximum subject tolerance. As the rehabilitation program progresses, the intensity of NMES will be changed as the subject's maximal tolerable level (Fig. 3D). Exercise data using the device will automatically be stored on the device and will be used for analysis.

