### Statistical analysis

2.11

The analysis will be described for all results included in the study. Quantitative outcomes will be expressed with their mean ± standard deviation, and qualitative results will be described with their absolute value, percentage, and 95% confidence intervals.

Data will be analyzed using SPSS V.22.0 software. To observe the associations between the qualitative variables, *χ*2 test will be used. Before comparing the means, Kolmogorov–Smirnov test and the Levene test will be used to confirm the normal distribution and homogeneity of the variances of the quantitative variables. For variables with normal distribution, Student t-test will be used; for variables with a non-normal distribution, Mann–Whitney test will be used. Analysis of variance mixed model will be used to estimate of the average effect (differences between groups) for all variables. This analysis model incorporated the groups (intervention and control group), time (baseline, 2 weeks and 6 weeks), and the group × time interaction. When a significant *F* value is found, the Bonferroni post-hoc test will be applied to identify the differences. The size of the effect between the groups for the variables that present intergroup differences can be calculated at some point, with 95% confidence intervals. The level of statistical significance adopted will be 5%. The analysis will be performed by an independent researcher.

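### Exercise frequency and duration is measured by device in one arm and by logbook in the other, so its planned group difference cannot separate exercise done from how it was recorded

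*Protocol article*

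**What the plan says.** Section 2.6.2 (Secondary outcome measures) defines the outcome as "Frequency and duration for exercise using data from device or exercise logbook". That line alone does not say which source serves which arm, but the two intervention sections do.

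- Section 2.5.2 (Intervention group): "Exercise data using the device will automatically be stored on the device and will be used for analysis".
- Section 2.5.3 (Control group): "An exercise logbook will also be provided to all subjects in the self-exercise group to record exercise frequency and duration". The same section says of the exercises: "All exercises in the control group are the same as in the intervention group, except the use of wearable device". The controls therefore have no device that could record them.

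Section 2.11 (Statistical analysis) then states: "Analysis of variance mixed model will be used to estimate of the average effect (differences between groups) for all variables". Exercise frequency and duration is one of those variables.

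The Introduction gives the hypothesis that this outcome most directly addresses: "We hypothesize that the incorporation of games and wearable technology into an exercise therapy program will improve patient motivation and compliance".

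**The concern.** A between-group comparison needs the outcome measured in the same way in both groups. Here one group is recorded by a sensor-based device and the other by its own entries. The two sources need not err alike. A logbook depends on what participants remember and choose to enter, and they know their arm. A device record depends on what the device is set up to capture and on its being worn. Assessor blinding, described in section 2.4, does not protect an outcome that no assessor measures.

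At stake is the reading of this one secondary outcome. A group difference could be taken as evidence that the device improves compliance, or a null result as evidence that it does not, when either could come from the change of instrument.

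**Working it through.** **Which instrument in which arm**

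| | Device record | Logbook |
|---|---|---|
| Intervention (2.5.2) | yes, stored automatically and used for analysis | none described |
| Control (2.5.3) | none, no device | yes |

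The filled cells lie on one diagonal. The document describes no logbook in the device arm, no sensor in the control arm and no calibration of one source against the other.

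**What the group term estimates.** Let μD and μC be the true mean amounts of exercise in the device and control arms. Let eD and eL be the mean errors of the device record and the logbook.

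- Observed device-arm mean = μD + eD
- Observed control-arm mean = μC + eL
- Observed difference = (μD − μC) − b, where b = eL − eD

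Only the observed difference is available, so the true difference and b cannot be told apart. More participants make the sum more precise without splitting it. A covariate for instrument would be identical to the group term. The group × time term in section 2.11 does not solve this. An offset that is constant over time would cancel from it, but what remains concerns change between visits rather than the level of exercise, and constancy of the offset could not be checked.

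**Numbers per arm.** Section 2.10.1 gives the only sample-size figures, and they are for strength: "the difference in the means of 6-week quadriceps strength was 33, with a standard deviation of 30", 5% two-sided significance and 80% power.

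- Normal approximation: n = 2 × [30 × (1.960 + 0.842) / 33]² = 12.97, so 13 per arm.
- Two-sample t-test: 14.00, matching the stated 14.
- With 30% attrition: 14 / 0.70 = 20, matching the stated 20.

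These figures reproduce and are not in dispute. They are used below only for the numbers per arm. The protocol gives no effect, standard deviation or sample size for exercise frequency or duration.

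**Illustration.** The value of b is not in the documents, so a range is assumed, in standard deviation units. The calculation is a two-sided 5% two-sample t-test at one time point, with equal standard deviations, m per arm, 2m − 2 degrees of freedom and non-centrality (true difference − b) × √(m/2).

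With no true difference in exercise, the chance of a significant group difference in either direction is:

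| Assumed size of b | 20 per arm | 14 per arm |
|---|---|---|
| 0.25 | 12% | 10% |
| 0.50 | 34% | 25% |
| 0.75 | 64% | 48% |
| 1.00 | 87% | 72% |

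For example, at b = 0.5 and 20 per arm the non-centrality has size 0.5 × √10 = 1.58 on 38 degrees of freedom, which gives 34% against the nominal 5%.

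With an assumed true advantage of 0.5 for the device arm and 20 per arm, the chance of detecting it is 34% if b = 0. If the logbook reads higher than the device by 0.25, it falls to 12%; by 0.5, to 2.5%. If the logbook reads lower than the device, b is negative and the apparent advantage is inflated instead.

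**The case against.** Several points can fairly be made for the plan.

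- **Weight.** This is a secondary outcome in a trial that section 2.10.1 calls exploratory. The primary outcome is dynamometer strength, and the hypothesis in the Discussion (section 3) concerns quadriceps strength. The compliance hypothesis is in the Introduction. All of this stands, and it limits the importance of the point.
- **Condensed article.** A journal article may leave measurement detail to the full protocol. That does not answer this point, because the article itself assigns a source to each arm.
- **Clinic visits.** Section 2.5 has exercise status checked in both arms at 2, 4 and 6 weeks. This is a common contact, but it is not defined as an outcome measure and gives no frequency or duration to analyse.
- **Objective data.** The Introduction values device data as a more objective form of monitoring. That is a good reason to keep and report the data. It does not make them comparable with a logbook.

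A reader might go further and infer that logbooks will overstate and the device will under-count, so that a real benefit is likely to be hidden or reversed. The documents do not support this. A logbook can also omit sessions. Section 2.5.2 has home exercise in the device arm performed with the device, and nothing says how much exercise, if any, goes unrecorded. A reader might also try to size the bias from the 35% to 76% compliance range in the Introduction. That range is a proportion of patients who comply, whereas the outcome is an amount of exercise. Turning over-reported amounts into a compliance rate would need a threshold and a distribution that the documents do not give.

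**Conclusion.** The point holds for this outcome. As the protocol describes it, arm determines instrument, and the planned group difference in exercise frequency and duration mixes true exercise with measurement difference. It cannot support a conclusion about compliance in either direction.

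The direction and size of the bias are unknown. The percentages in the working rest on assumed values of b, and one of them on an assumed true advantage. They show only that a moderate instrument difference would matter at this sample size. The conclusion assumes that the device arm keeps no logbook, which is the natural reading of section 2.5.3; if it does keep one, the protocol should say so.

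It would go too far to say that the trial's main question is compromised. The primary strength outcome and its sample size are untouched. The change is worth making because it is cheap and removes a bias that is built in.

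**What to change.** 1. Amend sections 2.5.2 and 2.6.2 so that participants still to be enrolled receive the same exercise logbook in both arms.
2. Base any between-group comparison of frequency and duration on logbook against logbook, restricted to participants of both arms randomised after the change. Section 2.2 says data collection is ongoing. Comparing later device participants with all controls would mix calendar time into the contrast, whereas a concurrent comparison keeps the randomisation.
3. Report device data for the device arm only, as a description and to show how far device and logbook agree within the same people.
4. Where no common logbook is available, including for participants already treated, report the two sources separately and descriptively, with no between-group test and no conclusion on compliance. If enrolment is nearly complete, this step may be all that is feasible.
5. Exempt this outcome from the statement in section 2.11 that group differences are estimated for all variables, except as in step 2.

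**Cost.** At most 20 further logbooks, a slight extra burden for device-arm participants, and an amendment reported and registered as section 2.13 provides. Keeping a log adds self-monitoring to the device arm. The comparison will have fewer than 20 per arm: for an assumed true difference of 0.5 standard deviations with no instrument bias, power is 34% at 20 per arm and 25% at 14. The data also remain unblinded self-report, and device users' entries may be informed by their stored usage data, so logbook against logbook reduces the problem without fully removing it. These limits should be stated with the result.
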